## Abstract

**Background:**

Hypertension is a clinical condition highly prevalent in the elderly, imposing great risks to cardiovascular diseases and loss of quality of life. Current guidelines emphasize the importance of nonpharmacological strategies as a first-line approach to lower blood pressure. Exercise is an efficient lifestyle tool that can benefit a myriad of health-related outcomes, including blood pressure control, in older adults. We herein report the protocol of the HAEL Study, which aims to evaluate the efficacy of a pragmatic combined exercise training compared with a health education program on ambulatory blood pressure and other health-related outcomes in older individuals.

**Methods:**

Randomized, single-blinded, multicenter, two-arm, parallel, superiority trial.

A total of 184 subjects (92/center), ≥60 years of age, with no recent history of cardiovascular events, will be randomized on a 1:1 ratio to 12-week interventions consisting either of a combined exercise (aerobic and strength) training, three times per week, or an active-control group receiving health education intervention, once a week. Ambulatory (primary outcome) and office blood pressures, cardiorespiratory fitness and endothelial function, together with quality of life, functional fitness and autonomic control will be measured in before and after intervention.

**Discussion:**

Our conceptual hypothesis is that combined training intervention will reduce ambulatory blood pressure in comparison with health education group. Using a superiority framework, analysis plan prespecifies an intention-to-treat approach, per protocol criteria, subgroups analysis, and handling of missing data. The trial is recruiting since September 2017. Finally, this study was designed to adhere to data sharing practices.

**Trial registration:**

NCT03264443. Registered on 29 August, 2017.

**Electronic supplementary material:**

The online version of this article (10.1186/s12889-019-6970-3) contains supplementary material, which is available to authorized users.

## Backgrounds

Hypertension is a leading risk factor for disability-adjusted life years globally [1] and contributes to chronic diseases with low quality of life and high mortality rates. Advanced age and elevated blood pressure (BP) exponentially increase mortality risk, which underscore the importance of BP control in the older population [2]. Among nonpharmacological interventions, structured exercise programs are strongly recommended for adults with elevated BP or essential hypertension [3]. In older subjects, exercise interventions are cornerstone due to multiple effects that may benefit not only vascular disease markers [4] but also other outcomes related to physical function [5, 6].

Meta-analyses of several controlled intervention studies have generated estimates that, individually, aerobic or resistance exercise training can reduce systolic BP levels by 6 to 8 mmHg in patients with hypertension [7, 8]. However, two main aspects limit extended evidence extrapolation. First, trials have mostly used either aerobic or resistance exercise training alone in young or middle-aged individuals without hypertension. Second, given that the combination of aerobic and resistance training has become a recommended mode of exercise training, it is relevant to investigate the efficacy of combined training in older individuals with hypertension. Although combined exercise programs can enhance the nonpharmacological treatment of hypertension in the elderly, such sample has been scarcely addressed in clinical trials [9, 10]. Moreover, inferences are considerably constrained by only a minority of studies examining BP as a primary outcome together with a high risk of bias indicated by lower-to-median scores of methodological quality [9].

We aim to evaluate the efficacy of a combined aerobic and resistance exercise training program on reducing BP levels compared with an attention control group undergoing health education in older patients with hypertension (≥ 60 years old). Herein, we will describe the HAEL Study, which is a parallel, randomized (1:1 allocation ratio), controlled by active intervention, blinded for outcome assessors and data analysts, multicenter, superiority trial, using ambulatory BP as the primary outcome. The choice of the active comparator group aims to reach a principle of equipoise and partially account for research participation effects (Hawthorne effect). Our main hypothesis is that the exercise training program will lead to greater reduction in systolic ambulatory BP in comparison to the control group. Secondary outcomes related to cardiovascular, mental, and physical function were chosen due to their relevance for the elderly. Based on the design of interventions and variables of interest, we hypothesize that the combined exercise training program will lead to superior changes in secondary outcomes when compared to the health education.

## Methods

### Study setting

This multicenter trial takes place in Porto Alegre and Pelotas, cities located in southern Brazil. Porto Alegre is the coordinator center, at the Hospital de Clínicas de Porto Alegre, and centralizes most of the methodological procedures discussed below. The research teams for each center have similar sizes and identical structures of investigator roles (Additional file 1). The equipment and space used for interventions at both centers are similar and will be detailed in the *Interventions* topic. The present study protocol follows as closely as possible the SPIRIT Statement 2013 [11]. The World Health Organization Trial Registration Dataset is provided herein (Additional file 2).

### Eligibility criteria

Inclusion and exclusion criteria for subjects are defined as follows. Study centers were chosen by convenience and no eligibility criteria was defined a priori for care-providers:

#### Inclusion criteria

Diagnosis of hypertension as assessed by a previous ambulatory BP monitoring (no later than six months) or current use of anti-hypertensive drugs.Age ≥ 60 years old.Unchanged pharmacological scheme for four weeks prior enrollment.Willingness to participate in either intervention group.

#### Exclusion criteria

Inability or unwillingness to give informed consent for participation.Myocardial infarction, revascularization procedures, deep vein thrombosis, cerebrovascular events or pulmonary embolism within the last 12 months.Presence of chronic heart failure with NYHA classes III or IV or unstable arrhythmia.Presence of chronic lung disease requiring use of corticosteroid or oxygen therapies.Consumption of more than 14 alcoholic drinks per week.Presence of kidney disease requiring dialysis.Language, hearing or cognitive issues limiting communication.Plans to move outside the areas of HAEL study sites during the period of participation.A friend or relative living in the same household is a study participant.Presence of progressive neurological disorders (Parkinson’s disease, multiple sclerosis, etc.)Cancer requiring treatment within the past two years.Medical report indicating moderate or high risk for exercise-related event [12], based on the initial maximal exercise test and clinical evaluation.

### Interventions

The HAEL participants are randomly allocated either to a combined exercise training program or to a health education intervention, each lasting 12 weeks. Detailed description on both interventions is provided below:

#### Combined exercise training

In Porto Alegre, exercise sessions take place at a communitarian exercise facility external to the teaching hospital. In Pelotas, exercise sessions take place at an exercise facility within the School of Physical Education, Universidade Federal de Pelotas.

Supervised exercise sessions lasting approximately 60 min, 3 days per week. The session consists of an initial warm-up (< 5 min), followed by 20–30 min of aerobic exercise in moderate intensity, 4–5 exercises, 2–3 sets of resistance training (lasting from 15 to 20 min), and 5–10 min of cool-down. The intensity of walking/running is based on the original Borg rating at 12–14 of perceived exertion [13], whereas resistance exercises are based on OMNI rating of 4–8 (out of 10) of perceived exertion scale [14]. Prescribed movements are identical for both centers and consist of multi-joint resistance exercises emphasizing major muscle groups and daily-life activities like sitting, standing up, pushing and pulling. To achieve greater external validity and applicability in environments with limited resources, the exercises are based on bodyweight and elastic band resistance, which require low complexity for setting up, are affordable and can be performed in limited space. The last 5–10 min of each session serve as the cool-down period, during which subjects perform stretching and mobilization exercises. During this time, the exercise supervisor addresses one of hypertension-related topics, based on the same contents planned to the health education group, however, with a brief informative approach lasting 2 to 5 min. Progression for resistance training sessions is based on more intense and faster contraction speed (Table 1). BP measurements are carried out before every exercise session to ensure that subjects BP are below 180 and 100 mmHg for systolic and diastolic BP, respectively. These pre-exercise BP values are documented once a week in subject’s records.

**Table 1 Tab1:** Resistance training prescription within the combined exercise program

Resistance training variable	Initial prescription (weeks)	Progression (weeks)
Number of sets	2 (1–3)	3 (4–12)
Intensity^a^	Light to moderate (1–3)	Moderate to high (4–12)
	Target: 4 to 6, out of 10	Target: 6 to 8, out of 10
Number of exercises	4 (1–6)	5 (7–12)
Contraction speed^b^	Moderate (1–6)	High (7–12)

^a^assessed by OMNI rating of perceived exertion scale. ^b^concentric contraction performed as fast as possible

#### Health education

In Porto Alegre, this intervention takes place at the Center of Clinical Research at the Hospital de Clinicas de Porto Alegre. In Pelotas, the intervention takes place at the School of Physical Education, Universidade Federal de Pelotas. The intervention consists on educational program with weekly lectures of approximately 60 min of duration. Each lecture is led by health professionals who follow a content script unified for both centers. By using expositive and interactive approaches, topics cover basic knowledge related to hypertension and therapeutic management. Table 2 shows all topics addressed in the health education group. Before the weekly education sessions, participants’ BP levels are measured and documented.

**Table 2 Tab2:** Topics covered in the health education intervention

Topics in health education for hypertension	
1.Getting to know hypertension	
2. Hypertension and risk	
3. Signs, symptoms and urgencies	
4. General treatment for hypertension	
5. Medication and adherence	
6. Diet-sodium intake	
7. DASH diet	
8. Alcohol and tobacco	
9. Psychological stress	
10. Weight loss and risk reduction	
11. Physical activity	
12. Wrap-up and celebration	

*DASH:* Dietary Approaches to Stop Hypertension

#### Hypertension management

For safety reasons, some criteria are implemented to manage participants with uncompensated BP along the study (Fig. 1). Participants allocated to any intervention arm presenting sustained pre-session systolic or diastolic BP equals to or greater than 180 mmHg or 100 mmHg, respectively, at two subsequent sessions must undergo a medical appointment. Such values are defined by at least two measurements per session for participants in both groups. In addition, participants in combined exercise training are invited to walk for 5 min at light intensity to reduce a possible anticipatory BP elevation prior the exercise; in these cases, measurements occur after due rest after such short walk episode.

**Fig. 1 Fig1:**
[figure not shown]
Decision tree algorithim for incidence of excessively high resting blood pressure values before intervention sessions. * indicates values of systolic and diastolic blood pressure, respectively

Therefore, participants with elevated BP according to the cutoff values mentioned above should be examined within seven days through consultation carried out by participants’ physicians or study cardiologists. In consultations provided by study cardiologists, an algorithm will be followed (Fig. 1). In brief, whenever a consultation occurs, participants should receive medical clearance to continue to participate. In appointments conducted by study cardiologists, no pharmacological adjustment will be made at a first appointment for participants receiving medical clearance. Therefore, such consultations will be based on reinforcing measures of antihypertensive management. Whenever a second medical appointment is necessary, pharmacological adjustments will be considered to ensure BP control and risk reduction. Such cases may fulfill criteria for discontinuation and will only be kept in interventional under medical recommendation.

#### Criteria for discontinuing allocated interventions

A participant may be discontinued from the study at the investigator’s discretion for safety reasons. For subjects allocated to any group, an incident cardiovascular event, hospitalization or severe health event during the intervention period are considered criteria to discontinue study participation. Examples of a severe health event may include: sustained uncompensated BP for 2–3 times during the protocol (systolic BP ≥ 180 mmHg or diastolic BP ≥ 100 mmHg, respectively), and medical illness that precludes attendance to intervention sessions. In addition, muscular or joint injuries (e.g., muscular, joint) impairing the participant to follow the intervention are considered exclusion criteria for participants allocated to combined exercise training.

#### Strategies for trial retention

During weekends, participants allocated to both groups receive text messages with Institutional Review Board (IRB)-approved content to reinforce time and place of intervention sessions. For the health education group, the message content is based on the topic that will be covered at the next class, whereas the exercise training group receives four slightly different messages along each month of intervention (three monthly cycles of four messages). We use phone calls to inquire for any adverse events if a participant misses a session of any intervention arm. The phone calls schedule is ceased for participants declaring their withdrawal from the study.

### Outcomes

In each center, both randomized groups are assessed for the outcomes listed below by standardized methodological procedures and a similar schedule (Table 3). Outcomes are measured for all randomized participants, irrespective of attendance or completion status. For participants who drop out of the study at any time after the randomization, research personnel use contact information to invite such individuals to undergo the end-study outcome assessments (12 weeks after intervention onset).

**Table 3 Tab3:** Time scheme for study conduction

	Study period							
	Enrolment	Baseline measures	Allocation and run-in^*^	Post-allocation			Close out	
TIMEPOINT**➔**	t-1	t0	t1	t2	t3	t4^†^	t5^†^	t5^†^
*Timepoint description*	Interviews	Occurs in 2 or 3 evaluation visits	–	Intervention Start	Evaluation visit (6th week)	Intervention end	Final evaluation visit 1	Final evaluation visit 2
ENROLMENT:								
Eligibility screening	x							
Informed consent	x							
Allocation			x					
INTERVENTIONS								
Combined exercise program				x	x	x		
Health education program				x	x	x		
ASSESSMENTS								
*Primary outcome*								
Ambulatory blood pressure		x					x	
*Main secondary outcomes*								
Office blood pressure		x					x	
Endothelial function^‡^		x			x		x	
Cardiorespiratory fitness^§^		x						x
*Other outcomes*								x
6-min walking test distance		x						x
SPPB		x						x
Quality of life questionnaires		x					x	
Autonomic function^‡^		x					x	
*Additional measurements*								
Anthropometric measurements		x					x	
Medication adherence scale (MMAS-8 Questionnaires)		x					x	
Blood variables collection		x					x	
Self-reported physical activity		x			x		x	
Grip strength		x			x			x

*SPPB* Short physical performance battery; *MMAS* Morisky Medication Adherence Scale. * = run-in period will be no longer than 2 weeks. † = time between t4 and t5 will be no longer than 2 weeks. ‡ = analysis of blood pressure and heart rate variability, exclusive for data collected at the coordinator center; § = cardiorespiratory fitness assessment occurs in a third separate visit at the participating center. Use of the©MMAS is protected by US copyright and registered trademark laws. Permission for use is required. A license agreement is available from [name], [name]; [contact]

#### Primary outcome

The primary study outcome is systolic BP assessed by 24 h ambulatory BP monitoring measured before and after three months of intervention. Systolic BP was chosen as the primary outcome due to its linear rise in relation to age and powerful prediction of cardiovascular events in older adults [15, 16]. The study timeframe was chosen to allow an adequate time range to effects (if any) take place, while optimizing trial logistics and participants adherence to interventions [7].

The ambulatory BP values will be treated as individual values for diurnal (from device placement to 10 PM, within the evaluation day), nocturnal (from reported sleep time to reported waking time) and 24 h periods, aggregated as group means at baseline and 12 weeks (trial end). Baseline measurements are carried out no longer than 30 days before the first intervention session whereas post-intervention assessment occurs within 10 days after the last session.

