#### Measurement of primary outcome

##### Ambulatory BP

In the assessment of 24-h BP, subjects wear an ambulatory BP monitor (90,207, SpaceLabs, Redmond, WA, USA) on the non-dominant arm for 24 h. Participants are asked to refrain from exercise the day prior to and during the recording period. While wearing the monitor they are also asked to maintain a diary of daily activities to record any abnormal activities (such as highly stressful situations, increased physical exertion, etc.) and sleep hours. Data on self-reported sleep times will be used to analyze daytime and nighttime patterns of ambulatory BP monitoring. Ambulatory BP exams are considered valid when at least 70% of the expected readings are available, otherwise, an additional measurement is necessary [29]. Subjects allocated to the combined training intervention undergo the ambulatory BP assessment at least 24 h and no later than 10 days after the last exercise session.

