### Statistical considerations

For primary and secondary outcomes, we will adhere to the intention-to-treat (ITT) principle and analyze all randomized participants, irrespective of attrition. The primary hypothesis will be tested on a superiority framework. Variables from ambulatory BP will be treated as diurnal, nocturnal and 24-h for both systolic and diastolic BP. Mixed effects models will be used to determine differences between groups using final values for systolic and diastolic ambulatory BP, adjusted for baseline values (pre-intervention). If these data present low linear fit, we will compare groups using generalized estimating equations with an independence model as the covariance matrix.

Two analysis sets will be established as follows: (1) a full analysis set (FAS) including all randomized subjects, therefore allowing ITT analyses; and (2) a per-protocol (PP) analysis set including all subjects that completed the trial (completers) with adherence to at least 70% of the intervention sessions (≥ 25 sessions for participants allocated in the exercise program, and ≥ eight sessions for participants allocated to the education program). Participants that drop out of the study due to safety concerns or other outcomes will not be censored in PP analysis. Additionally, we plan to carry out a subgroup analysis stratifying both groups by individuals with non-controlled BP before the intervention versus individuals with well-controlled BP before the intervention. Such stratification will be based on tertiles of systolic BP at baseline, with a primary interest in the comparison of interventions on ambulatory BP using the lowest and highest thirds.

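### The diurnal period ends at a fixed 10 PM while the nocturnal period follows the diary, so the two overlap or leave gaps and next-morning waking readings enter only the 24-h mean

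*Protocol article*

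**What the plan says.** Four places in the protocol article bear on this.

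- **Primary outcome, the endpoint.** "The primary study outcome is systolic BP assessed by 24 h ambulatory BP monitoring".
- **Primary outcome, the periods.** Three are defined. The day is "diurnal (from device placement to 10 PM, within the evaluation day"; the night is "nocturnal (from reported sleep time to reported waking time"; the third is the whole recording, "and 24 h periods, aggregated as group means at baseline and 12 weeks (trial end".
- **Ambulatory BP (Measurement of primary outcome).** The monitor is worn "on the non-dominant arm for 24 h", and participants keep a diary that includes sleep hours. The section then states: "Data on self-reported sleep times will be used to analyze daytime and nighttime patterns of ambulatory BP monitoring". It does not mention 10 PM.
- **Statistical considerations.** "Variables from ambulatory BP will be treated as diurnal, nocturnal and 24-h for both systolic and diastolic BP". Final values are compared between groups with adjustment for baseline.

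The Main secondary outcomes section also lists diastolic BP, measured by ambulatory and office methods. The Sample size section states power for 24-h systolic BP only.

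**The concern.** The two sub-periods are cut by different kinds of boundary. The day ends at a clock time that is the same for everyone, and the night starts at a time that each participant reports. They meet cleanly only for someone who falls asleep at exactly 10 PM. The day is also confined to the evaluation day and the night stops at waking, so the waking hours of the second morning belong to neither.

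The Ambulatory BP section points to a different rule, with sleep times used for daytime as well. Two analysts, one working from each section, could compute different diurnal means from the same recording.

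What is at stake is the quality of the diurnal and nocturnal variables. These are analysed for both systolic and diastolic BP in a trial that its Discussion describes as confirmatory. If the diurnal mean covers different hours in different people, or in one person at baseline and at 12 weeks, the baseline adjustment sets unlike quantities against each other and precision suffers.

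**Working it through.** **The plan's own figure first.** The Sample size section gives power of 0.79 and 0.92 for differences of 2.5 and 3.0 mmHg, with SD 6.0, 184 participants and two-sided alpha 0.05. With power = Φ(δ/SD × √(n/2) − 1.96):

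- n = 184/2 = 92 per arm: 2.5/6 × √46 = 2.826, power 0.807; 3.0/6 × √46 = 3.391, power 0.924.
- n = (184 − 22)/2 = 81 per arm, with variance reduced by the stated intraclass correlation of 0.1 (SD = 6 × √0.9 = 5.692): power 0.798 and 0.918.

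Both readings come within 2 percentage points of the stated values. Neither uses the 10 PM cut or a sleep time, because the power is for the 24-h mean. The issue therefore does not touch it.

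**The windows.** Let P be the time of device placement, S reported sleep and W reported waking, on a clock that runs past midnight (07:00 next day = 31). The recording ends at P + 24. The Primary outcome definitions give diurnal = P to 22 and nocturnal = S to W. Then:

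- hours in both sub-periods = max(0, 22 − S)
- evening hours in neither = max(0, S − 22)
- next-morning hours in neither = max(0, P + 24 − W)

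**Illustrations.** P, S and W are assumptions, because the document gives none of them.

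| Fitting | Sleep | Waking | Counted twice | Evening gap | Next morning | Outside both |
|---|---|---|---|---|---|---|
| 10:00 | 23:00 | 07:00 | 0 h | 23 − 22 = 1 h | 34 − 31 = 3 h | 4 of 24 h (17%) |
| 14:00 | 23:00 | 07:00 | 0 h | 23 − 22 = 1 h | 38 − 31 = 7 h | 8 of 24 h (33%) |
| 10:00 | 21:00 | 07:00 | 22 − 21 = 1 h | 0 h | 34 − 31 = 3 h | 3 of 24 h (12.5%) |

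The diurnal window lasts 22 − P: 12 h when fitted at 10:00 and 8 h when fitted at 14:00. As a check on the first row, 12 h diurnal + 8 h nocturnal + 4 h outside = 24 h.

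**Range.** With fitting from 08:00 to 12:00, sleep from 21:00 to midnight and waking at 06:00 or 07:00, between 1 and 8 h fall outside both sub-periods (about 4% to 33% of the recording). Up to 1 h is counted twice. The reading interval is not given, so these are hours and cannot be turned into numbers of readings.

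**Under one diary rule.** If diurnal is everything in the recording outside S to W, overlap and unassigned time are both 0 h for any P, S and W.

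**The case against.** The strongest reply has four parts.

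1. **Nothing is discarded.** A reader might infer that the gap and next-morning readings are lost to the trial. The text does not support that. The Primary outcome section keeps a separate 24-h period, and nothing excludes these readings from it. This part stands in full.

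2. **The primary comparison is intact.** Because the definitions sit under Primary outcome, a reader might infer damage to the main test. The endpoint is 24-h systolic BP and the power is stated for it; neither depends on how the day is split. This also stands.

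3. **No bias is shown.** The same rule applies to both arms, assessors and analysts are blinded, and procedures are standardised with a similar schedule and written operating procedures. A biased group difference would need fitting or sleep times to differ by arm at the final visit, and nothing in the document says that they do. This stands: what is shown is variable coverage, which means noise.

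4. **The two sections can be read together.** The Ambulatory BP sentence describes a use of sleep times in general terms. It sets no daytime window, and Primary outcome does use sleep times for the night. Nor does the document require that day and night sum to 24 h. This stands only in part. The conflict between the sections is one of wording, but the overlap and the gaps follow from Primary outcome alone. No reason is given for pairing a clock end with a diary start or for leaving out the second morning.

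It could also be said that such detail belongs in an analysis plan. But the article does not leave the definition open: it states one, and that definition yields the overlap and the gaps.

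**Conclusion.** The point holds for the diurnal and nocturnal variables. As defined, the sub-periods overlap for those asleep before 10 PM and leave an evening gap for those asleep later. They also leave out the second morning's waking hours, which enter only the 24-h mean. The diurnal means thus cover hours set partly by fitting and sleep times, and for early sleepers they include sleep. The expected harm is added noise in analysed variables other than the primary outcome, and a definition that two analysts could apply differently.

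That the definitions conflict needs no assumption about times; the size does. Over the assumed times shown, 1 to 8 of 24 h lie outside both sub-periods and up to 1 h is counted twice. Whether fitting time really differs between a participant's two recordings is unknown: the article does not fix it, though an operating procedure may. The correction is worth making before analysis, since it is cheap, but it is not a threat to the trial's main conclusion.

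**What to change.** State one rule, in the same words, in the Primary outcome and Ambulatory BP sections:

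- nocturnal: all valid readings between reported sleep time and reported waking time;
- diurnal: all other valid readings in the 24-h recording, including those of the next morning;
- 24-h: all valid readings.

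This is not the only workable rule, but it fits the sleep diary already collected and what the Ambulatory BP section already implies. The cost is the change of wording and a rerun of the reading classification on stored recordings. No new data are needed, and the sample size, the power and the 24-h primary analysis stay as they are.
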